### Interventions

#### Usual care

All participants in this trial will participate in the usual care structure of rehabilitation at the treating institution. Under the usual care rehabilitation, inpatients at the hospital with TKA attend either two 45-min sessions of physiotherapy or one 45-min session of physiotherapy and one 45-min session of hydrotherapy every day on five days of the week. All participants also attend one 45-min session of either physiotherapy or hydrotherapy on the other two weekend days. All patients at the rehabilitation hospital receive hydrotherapy unless the surgeon recedes permission, or for health or personal preferences of the patient. The hydrotherapy exercises use water resistance, buoyancy and hydrotherapy equipment to achieve the same goals as the land-based therapy. Patients who do not receive hydrotherapy will attend an additional session of land-based physiotherapy, meaning that all patients receive exercise therapy twice a day. Participants will be given a home exercise program to be completed following discharge from inpatient rehabilitation. The home exercise program will be identical to the exercises performed during inpatient rehabilitation. Exercise dosage will be recorded in an exercise diary.

Participants will return to the rehabilitation hospital to participate in the outpatient rehabilitation program approximately one week following discharge from inpatient rehabilitation. All participants will attend once per week for one 45-min session of physiotherapy and either one 45-min session of hydrotherapy (if indicated) or land-based exercise (if hydrotherapy not indicated). These two 45-min sessions will occur consecutively on the same day of each week. Participants will continue their home exercise program and complete their diaries daily.

The exercises in the usual care rehabilitation program are representative of usual care following TKA, and are described in detail in Table 1 and in the Additional file 1. The goals of the usual care rehabilitation program are to improve quadriceps, hamstring and calf strength, to increase knee range of movement and to improve walking and stair climbing ability. Manual therapy including joint mobilization and massage may also be used in addition to exercises to achieve these goals.

**Table 1 Tab1:** Usual Care Exercises

Goal	Exercise
Improve quadriceps strength	Static quads
	Quads over fulcrum
	Forward step-ups
	Squats
	Leg press
	Forward step-downs
Increase active knee flexion ROM	Hip and knee flexion
	Knee flexion in sitting
	Seated slides
	Exercise bike
Improve hamstring strength	Hamstring curls in prone
	Hamstring curls in standing
Increase knee extension ROM	Prone hanging
	Knee extension stretch in sitting
Improve calf muscle strength and flexibility	Heel rises
	Calf stretch

#### Intervention group

Participants in the intervention group will receive the usual care program of rehabilitation. They will also receive 15 min of additional exercises at each physiotherapy session (total time of 1 h, twice per day) designed specifically to target strengthening of the hip abductor muscles.

The following exercises are unique to the hip strengthening group and have been selected after a review of the literature investigating the efficacy of various hip abductor strengthening exercises (Table 2 and Additional file 1) [18, 19, 24–27]. They will be performed in addition to usual care received following TKA at the rehabilitation hospital. The participants will initially perform non-weight bearing antigravity hip strengthening exercises, such as sidelying hip abduction, prone hip extension, standing abduction. The exercises will be progressed to weight bearing, gravity-resisted exercises such as sideways walking, and hip abduction whilst standing on the operated leg. If the participant receives hydrotherapy they will perform the same additional hip strengthening exercises in the water, to address the identical goals of the land based program.

**Table 2 Tab2:** Additional Hip Strengthening Exercises (Intervention Group)

Goal	Exercise
Improve hip strength	Sidelying hip abduction
	Prone hip extension
	Sideways walking
	Standing hip abduction
	Hip hitching

#### Control group

The participants in the control group will receive the usual care program of rehabilitation and will also receive an additional 15 min of exercise at each physiotherapy session (total session time of 1 h, twice a day) to act as a time control for the additional hip strengthening exercises prescribed for the intervention group (Table 3 and Additional file 1). These exercises have been designed to replicate functional activities such as sit-to-stand, marching and walking around a pre-measured circuit. If the participant receives hydrotherapy they will perform the same additional exercises in the water.

**Table 3 Tab3:** Additional Usual Care Exercises (Control Group)

Goal	Exercise
Improve general function	Sit to stand
	Marching
	Walking

### Delivery of the intervention

Due to the physical nature of the intervention, the treating physiotherapists will not be blinded. Physiotherapists currently employed at the rehabilitation hospital will provide the interventions. The professional qualifications, years of practice and specific training prior to trial initiation will be recorded. All physiotherapists will attend a training session to ensure the exercises are performed accurately and progressed appropriately. At this training session correct and incorrect performance of the exercises will be demonstrated. Exercises will be progressed when able to be completed with minimal fatigue and no significant increase in pain. The physiotherapists will be provided with a detailed manual describing the exercise programs and progression. Follow-up training sessions will be held with the physiotherapists to ensure consistency and address any issues that may arise. Consistency and adherence will also be monitored by the recording of treatment in the participants’ medical record. The medical record includes each exercise performed, the number of repetitions of each exercise performed, any variations in the exercises performed and reasons for any variations such as adverse effects.

### Performance quality

Performance quality will be monitored by the physiotherapist. The physiotherapist will reassess each participant at the start of each session, and the exercises modified accordingly. If there are significant increases in pain (Visual Analogue Scale = 5 or greater) the physiotherapist will use his/her clinical reasoning to reduce intensity of particular aggravating exercises or add specific manual physiotherapy treatment as required. To ensure that appropriate muscle adaptation is achieved, the participant’s exercises will be progressed according to the American College of Sports Medicine (ACSM) guidelines [28] as soon as the patient is able, and details and criteria for this progression are described in the Additional file 1.

The treating physiotherapist will record the details of each treatment session, and will include the type of exercises and dosage. Any changes to the exercises or adverse responses will be noted. Following discharge from inpatient rehabilitation, participants will be given a home exercise program to continue their exercises and a diary to record daily exercises. The exercises will be progressed during the outpatient phase and the diary used to record dosage and completion of exercises. On discharge from outpatient rehabilitation, the participants will continue to complete the home exercise program until the 6-month follow-up.

### Outcome measures

Demographic information to be collected from all participants includes: name, age, gender, height, weight and body mass index. The type of prosthesis used (including patella resurfacing), left/right TKA, previous joint replacements, co-morbidities, social history (including place of accommodation, occupation/retired), co-interventions (e.g. hydrotherapy), length of hospital stay, number of treatment sessions and analgesics used will be recorded.

The measures that will be used to assess outcome are summarized in Table 4. The primary outcomes measures are: Knee Injury and Osteoarthritis Outcome score (KOOS) and isometric hip abductor muscle strength. The secondary outcome measures are: Stair Climb Test, 6 min walk test, Timed Up and Go, 40 m fast-paced walk test, 30-second chair stand test, step test, isometric quadriceps muscle strength, Lower Extremity Functional Scale (LEFS) and SF-12. These physical performance measures were selected based on the recommendations from Osteoarthritis Research Society International (OARSI) for older patients (>40 years old) diagnosed with hip and/or knee OA [29].

**Table 4 Tab4:** Outcome measures

Outcome	Measurement
Knee Injury and Osteoarthritis Outcome Score	Pain, other symptoms, function and quality of life
Isometric strength of hip abductors	Hand held dynamometer (Newtons)
Stair climb test	Total time (sec) to ascend and descend 4 steps.
6 min walk test	Distance (m) walked in 6 min
Timed Up and Go	Timed rise from chair, walk 3 m and return to sitting position.
40 m fast-paced walk test	Time (sec) taken to walk 40 m
30-second chair stand test	No. of sit-to-stands performed in 30 seconds
Step test	Number of step taps on a step in 15 seconds
Isometric strength of quadriceps	Hand held dynamometer (Newtons)
Knee ROM	Goniometer (degrees)
Lower Extremity Functional Scale	Lower extremity functional status
SF-12	Overall Health
Other measures	
Compliance	Therapist treatment records and patient diary
Adverse effects	Therapist treatment records and patient diary
Type of TKR	Operation report or surgeon contact

Primary and secondary outcomes will be measured at admission to inpatient rehabilitation (approximately 7 days post-operatively), 3 weeks, 6 weeks and 6 months after commencing the rehabilitation program. A discrepancy is often reported in the recovery of patient reported outcomes compared to functional performances, with the more rapid improvement noted in patient reported outcome scales while functional performance measures are often significantly reduced in the early post-operative period [30]. Therefore, the two types of outcome measures have been included to ensure an accurate representation of rehabilitation outcomes following TKA.

### Primary outcome measures

#### Knee injury and osteoarthritis outcome score (KOOS)

The Knee Injury and Osteoarthritis Outcome Score (KOOS) is a self report questionnaire with 42-items in 5 separately analyzed subscales of pain, other symptoms, function in daily living, function in sport and recreation, and knee–related quality of life [31]. The tool has good test-retest reliability with ICC _(2,1)_ values in 26 patients 6 months post TKA of 0.73 (QOL), 0.74 (Sport/recreation), 0.82 (ADL), 0.85 (Symptoms), and 0.94 (Pain). Good content validity demonstrated by 90 % of patients who regarded improvement in the subscales Pain, Symptoms, Activities of Daily Living, and knee-related Quality of Life to be extremely or very important when deciding to have their knee operated on. The KOOS is responsive on all subscales particularly the knee-related Quality of Life subscale (effect size 2.86 at 6 months post TKA and 3.54 at 12 months post TKA) [32].

#### Isometric strength of hip abductors

The hip abductors will be tested with the participant in supine with both hips in neutral abduction and rotation. A hand held dynamometer will be used to record force, in Newtons, generated during hip abduction as per the method described previously [33]. The hand-held dynamometer (HHD) will be placed 5 cm proximal to the lateral femoral condyle. Stabilization of the HHD will be achieved by wrapping a seatbelt around the HHD and securing it to a rail on the adjacent wall at plinth height. The participants will perform a maximal voluntary isometric contraction (MVC) by abducting their limb against the dynamometer and seatbelt, held for 5 seconds. The highest of three consecutive measures will be recorded as the MVC. This method of testing hip abductor strength was reliable and valid in a sample of patients similar to those intended for the current study [33]. The seatbelt will be used to resist hip abductor strength, as this method is less susceptible to the individual strength of the therapist [34].

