### Isometric strength quadriceps muscle

Isometric quadriceps strength will be measured against a strap and HHD with the patient sitting and the knee at 90° flexion [59]. Isometric quadriceps strength has been tested at knee flexion angles of 45-90° [60] and is recommended to be tested at 60-90° knee flexion [61]. Isometric quadriceps strength measured with HHD at 90° knee flexion has demonstrated excellent reliability (ICC _(2,1)_ = 0.96) and MDC_95_ of 0.58 N/kg following TKA [59]. If the participant cannot flex their knee to 90°, isometric quadriceps strength will be measured at the maximum range of flexion available and the range will be recorded. The hand-held dynamometer (HHD) will be placed on the anterior aspect of the distal tibia, 5 cm proximal to medial malleolus. Stabilization of the HHD will be achieved by wrapping a seatbelt around the HHD and securing it to a fixed attachment of the plinth. The participants will perform a maximal voluntary isometric contraction (MVC) by extending their lower leg against the dynamometer and seatbelt, held for 5 seconds. The highest of three consecutive measures will be recorded as the MVC.

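### The strength models ignore the baseline weight and height already collected, leaving body-size spread in the error of the group main effect for hip abductor strength, a primary outcome

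*Protocol article*

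**What the plan says.** Under the heading on isometric strength of hip abductors, the protocol article defines the primary strength measure: "A hand held dynamometer will be used to record force, in Newtons, generated during hip abduction". The highest of three contractions is kept. Table 4 gives the same unit, "Hand held dynamometer (Newtons", for the hip abductors and again for the quadriceps.

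The only numerical strength benchmark is in the quadriceps section, which says that the method "has demonstrated excellent reliability (ICC _(2,1)_ = 0.96) and MDC_95_ of 0.58 N/kg following TKA". The hip abductor section gives no figure; it says only "This method of testing hip abductor strength was reliable and valid in a sample of patients similar to those intended for the current study".

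The outcome measures section lists the demographic data to be collected: "name, age, gender, height, weight and body mass index". In the statistical section, BMI serves only to compare the groups at baseline. All outcomes are to be analysed by repeated measures ANOVA with group, time (baseline, 3 weeks, 6 weeks, 6 months) and their interaction. No covariate is named. The minimum sample is 82, for Cohen's f = 0.25, alpha 0.05 and power 0.8, and the recruitment target is about 104.

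**The concern.** Force measured at a pad 5 cm above the femoral condyle depends on body mass and thigh length as well as on muscle capacity. The trial enrols men and women aged 50 or older with no restriction on size, so part of the person-to-person spread in Newtons is probably body size. The group main effect is judged against exactly that spread. Unless the model accounts for size, this part counts as noise on a primary outcome, even though the variables that could remove it are already in the data set.

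A second, smaller matter is one of reading the result. The quadriceps outcome is in Newtons while its quoted detectable change is per kilogram, so no single Newton value corresponds to it.

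**Working it through.** **Inputs from the protocol article.** f = 0.25, alpha = 0.05, target power 0.80, N = 82, m = 4 time points (statistical section); quadriceps MDC95 = 0.58 N/kg (quadriceps section).

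**Assumed, because the article gives no figure.** Within-person correlation rho; the share R² of the variance of visit-averaged strength explained by weight and height; the coefficients of variation of force (CVf) and weight (CVw); the correlation r between weight and strength.

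**1. Which test does 82 belong to?**
- Group main effect: lambda = f²·N·m / (1 + (m − 1)·rho), with 1 and N − 2 degrees of freedom. At rho = 0.5 and N = 82, lambda = 0.0625 × 82 × 4 / 2.5 = 8.20 and power is 80.8%. At N = 80 power is 79.8%. So 82 is reproduced.
- Group-by-time interaction: lambda = f²·N·m / (1 − rho). At rho = 0.5 this needs only N = 24.
- The match depends on rho: the main effect needs 62 at rho = 0.3 and 100 at rho = 0.7.

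**2. Where does body size enter?** Take a person SD of 1, a residual SD of 1 and a stable additive size component with SD s. The expected between-person mean square is 4·(1 + s²) + 1, that is 5, 6 and 9 for s = 0, 0.5 and 1. A simulation with 82 participants and four visits gave 5.0, 6.0 and 9.1. The within-person mean square, which is the error for the interaction, stayed at 1.00 throughout.

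**3. Power of the main effect with size as a covariate.** For the same raw difference, lambda becomes 8.20 / (1 − R²).

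| Assumed R² | lambda | Power at N = 82, F(1, 80) | Power with two df spent, F(1, 78) |
|---|---|---|---|
| 0 | 8.20 | 80.8% | 80.7% |
| 10% | 9.11 | 84.7% | 84.6% |
| 20% | 10.25 | 88.5% | 88.5% |
| 30% | 11.71 | 92.2% | 92.2% |

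Spending the two degrees of freedom costs less than 0.1 percentage point, including when the covariates explain nothing.

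**4. Dividing by weight instead.** The variance of N/kg relative to that of N, on the squared coefficient of variation scale, is about 1 + (CVw/CVf)² − 2·r·(CVw/CVf). It falls below 1 only if r exceeds CVw/(2·CVf). For assumed CVf of 0.3 to 0.5 and CVw of 0.15 to 0.20, that threshold runs from 0.15/(2 × 0.5) = 0.15 to 0.20/(2 × 0.3) = 0.33. With CVf = 0.3 and CVw = 0.20 the ratio is 1.44 at r = 0 and 0.64 at r = 0.6. Scaling 82 by these gives 118 and 53. Ratio scaling can therefore help or harm, and the article does not show which.

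**5. The benchmark in Newtons.** 0.58 N/kg × 60, 80 and 100 kg = 34.8, 46.4 and 58.0 N.

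**The case against.** The strongest reply is that the interaction matters more than the main effect. Baseline is one of the four time levels, so a treatment effect that develops after baseline shows as group by time, and a stable additive size effect cancels from that error. This stands, and it limits the point to the main effect. It does not remove the point, because the plan tests main effects as well as interactions and the stated 82 fits the main effect. If size instead scales the gains multiplicatively, some of it would remain in the interaction error too.

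A second reply is that the size of the gain is assumed. That also stands: neither rho nor R² is in the article, and the planned f = 0.25 is a generic standardised effect supported by WOMAC results, not a strength difference in Newtons.

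A third is that a condensed article may leave scaling and covariates to a fuller document. The article does, however, state both the recorded unit and a model for all outcomes, and that model as stated has no covariate. Table 4 need not fix the reported scale, since it lists the 40 m walk in seconds while the text converts it to m/s. A derived strength scale is therefore not excluded, but none is stated.

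A reader might also infer that the detectable-change figure cannot be used at all, or that it undermines the primary outcome. Neither follows. Recorded weight allows conversion by one division, the figure concerns quadriceps only, and no passage uses it as a threshold.

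**Conclusion.** The point holds as one of efficiency. The stated model leaves body-size spread in the between-person error of the group main effect for hip abductor and quadriceps strength, although weight and height are at hand. Adjusting for them would raise main-effect power at 82 from 80.8% to about 85%, 88.5% or 92%, if they explain 10%, 20% or 30% of the variance of visit-averaged strength. This rests on rho = 0.5 and on the assumed R². Part of the gain would already be had if baseline strength were a covariate.

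Two stronger readings are not supported. Raw Newtons do not bias the comparison, because allocation is randomised. Nor is division by body weight a safe equivalent of adjustment: it can raise the variance when weight and strength are weakly correlated, and it leaves thigh length untouched. The difference in units is a minor matter of presentation for a secondary outcome.

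**What to change.** In the statistical section, keep both strength outcomes in Newtons and add baseline weight and height as prespecified covariates in the strength models. Centre both at their overall means, so that the time effect in the same model keeps its meaning.

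Report N/kg as a supportive scale only, so that the quadriceps detectable change, stated as "of 0.58 N/kg following TKA", can be read against the result. Do not make N/kg the primary scale. Fixing this before the data are unblinded also rules out a later choice between scales on a primary outcome.

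The cost is one sentence in the analysis section, one derived variable and two error degrees of freedom. No new measurement is needed.

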### Secondary outcome measures

#### Stair climb test

The stair climb test has been used extensively as an outcome measure in TKA [3, 13, 35–37]. The test assesses the time, in seconds, to ascend and descend a flight of stairs. The number of stairs in the flight and the step height are recorded. In the current study, a four-step staircase will be used. The use of a handrail and gait aids are permitted and will be recorded, as will be the footstep pattern (reciprocal or step-to). Inter-rater reliability was reported as ICC _(2,1)_ = 0.94 (95 % CI =0.55-0.98). MDC_90_ was calculated as 2.6 seconds [38]. The stair climb test has demonstrated adequate construct validity [39] and responsiveness detecting initial deterioration (effect size = −0.84) from pre-op to 1 month post-TKA scores, and then subsequent improvement (effect size = 1.26) from 1 month to 12 months post-TKA on a 12-step flight [36].

#### 6 Minute Walk Test (6 MWT)

The 6 min walk test (6MWT) is a frequently used measure for patients following TKA [3, 30, 35, 37, 40–45]. It is a test of aerobic capacity and long distance walking ability [29]. Patients are instructed to walk with usual gait aids on a premeasured circuit, covering as much distance as possible during the 6 min time frame. Rests are permitted and are included in the time. Test-retest reliability in participants with end-stage hip and knee OA awaiting joint replacement was calculated as ICC _(2,1)_ = 0.94 (95 % CI = 0.88-0.98) with standard error of measurement (SEM) of 26.3 m and MDC_90_ of 61.34 m [38]. The 6MWT is responsive when evaluating early recovery two to four months post TKA (effect size = 0.82, SRM = 1.51) [30].

#### Timed up and Go Test (TUG)

The timed up and go test (TUG) measures the time, in seconds, that a patient takes to stand from an armed chair, walk for 3 m, and return to sit on the same chair. A walking aid can be used if required [46]. The reliability of the TUG has been established in a study that combined pre-operative TKA and THA subjects. The test-retest reliability was reported as ICC _(2,1)_ =0.75 (95 % CI = 0.51-0.98) [38]. The TUG was found to be selective in its ability to distinguish healthy subjects from TKA patients [47]. It is responsive to detecting early deterioration and improvement in the early post-operative period with standardized response means (SRM) varying from −1.08 (95 % CI −1.38 to −0.92), indicating a worsening in the value to 1.04 (95 % CI 0.84 to 1.61) indicating an improvement in time taken to perform the test. Standard error of measurement (SEM) was calculated as 1.07 (95 % CI = 0.86-1.41) and minimal detectable change at the 90 % confidence level (MDC_90_) was 2.49 seconds [38].

